## Interventions

4

The patients will be guided to lay supine on a couch with their affected leg exposed. As shown in Figure 3A, the needling point will be at the ankle zone 5 of the affected leg. This point is located three fingers above the lateral malleolus and posterior margin.^[19]^

**Figure 3 F3:**
[figure not shown]
Photograph of the ankle acupuncture procedures and placement of acupuncture needles. The needling point at the ankle zone 5 of the affected leg. (A) The needle manipulation (Ankle acupuncture group, B and C). The needle manipulation (traditional needle manipulation group, D).

One certified acupuncturist with more than 5 years of clinical practice at each site will perform AA, sham AA, and TNM. The needle will be retained for 20 minutes and no manual needling manipulation will be conducted before the needle is withdrawn.

### AA group

4.1

After sterilizing with 75% ethanol at and around the needling point, a disposable sterile acupuncture needle (0.35 mm × 40 mm; Tianxie Brand, Beijing, China) will be used. The acupuncturist will hold the needle and swiftly insert it into the skin at the target point with a 30° angle to the skin. Then, the needle will be slowly advanced with a 0° angle to the skin until about 3/4 of the needle enters the subcutaneous tissue. The patients will not feel any *deqi* during this process if the AA is performed correctly. Then, the needle will be retained in the subcutaneous tissue for 20 minutes with the needle handle fixed to the skin with an adhesive tape (Fig. 3B and C).

### Sham AA group

4.2

A disposable sterile acupuncture needle (0.35 mm × 13 mm; Tianxie Brand) will be blunted before intervention so that it cannot be inserted into the skin easily. The skin will be sterilized as in the AA group. The acupuncturist will hold the blunt needle and prick the skin for 3 seconds, after which the needle will be pushed down to the skin. The needle will be retained for 20 minutes with the needle handle fixed to the skin with an adhesive tape.

### TNM group

4.3

After sterilizing with 75% ethanol, a disposable sterile acupuncture needle (0.35 mm × 13 mm; Tianxie Brand) will be used. The acupuncturist will hold the needle perpendicularly to the skin and swiftly insert to a depth of 2–3 cm into the skin at the target point. Then, the needle will be retained for 20 minutes without any movement (Fig. 3D).

## Outcome assessment

5

### Primary outcome measures

5.1

The primary outcome will be pain intensity on a VAS,^[30]^ with the primary endpoint at 0 minutes (immediately after treatment). The secondary time point will be at 2 hours after acupuncture treatment, and an area-under-curve analysis will be performed, including baseline, 15 minutes, 30 minutes, 3 days, and 7 days. We chose VAS because it is commonly used to measure pain intensity.^[31]^ The patients will be guided to mark a point on a 0 to 100 mm VAS, in which 100 (at the right end) indicates maximum pain and 0 (at the left end) indicates absolutely no pain.

### Secondary outcome measures

5.2

Given that paresthesia (e.g., numbness and tingling) is the second most common symptom in sciatica,^[32]^ the sensation will be measured as one of the secondary outcomes. Paresthesia intensity will be assessed using a 100-mm VAS, in which “0” indicates the absence of numbness and tingling and “100” indicates unbearable numbness and tingling.

The sensation of needling is one of the significant outcomes on reliability of the operation. The sensation of needling will be assessed using self-report measures after the needle is withdrawn. The participants will be asked to report any *deqi* sensation such as sourness, numbness, heaviness, warmness, and pain, among others.

Acceptability ratings will be obtained using the Abbreviated Acceptability Rating Profile (AAPR).^[33]^ In AARP, higher scores indicate greater acceptability. The reliability and validity of the Chinese version of AAPR are satisfactory.^[34]^

Any additional treatments received by participants will be asked to report at each follow-up.

Any severe adverse events such as bleeding, hematoma, or fainting during the acupuncture process will be observed and dealt with immediately. The needle will be removed once any of the above-mentioned severe events occur.

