**Method::**

This will be a double-blinded, randomized controlled clinical trial. Patients diagnosed with disc-related sciatica will be randomly divided into 3 parallel groups. The treatment group (n = 30) will receive ankle acupuncture. The 2 control groups will either undergo traditional needle manipulation (n = 30) or sham acupuncture (n = 30) at the same point as the treatment group. The primary outcome will be pain intensity on a visual analog scale (VAS). The secondary outcomes will be paresthesia intensity on a VAS and the Abbreviated Acceptability Rating Profile (AAPR). The success of blinding will be evaluated, and the needle-induced sensation and adverse events will be recorded. All outcomes will be evaluated before, during, and after the treatment.

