### Inclusion criteria

3.1

Patients will be included if they meet all of the following criteria: (1) age between 18 and 55 years (either sex); (2) primary complaint of unilateral leg pain radiating below the knee; (3) ipsilateral lumbar disc herniation at the corresponding level verified by MRI or computed tomography^[28]^; (4) duration of pain < 5 years; (5) pain intensity score of 40 mm or more on a 100-mm visual analog scale (VAS); (6) willingness and ability to accept needle-acupuncture intervention and to comply with the requirements of the study protocol; and (7) signed informed consent.

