### Exclusion criteria

3.2

Patients with any of the following conditions will be excluded: (1) leg pain originating from the upper lumbar column (L1–L3); (2) history of spine trauma or spine surgery; (3) history of stroke, heart diseases or severe hypertension, any endocrine diseases such as hyperthyroidism, and severe infection; and (4) other therapies, especially analgesics, in the past 7 days.

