### Statistical analysis

6.2

The Statistical Package for the Social Sciences (SPSS version 21.0) will be used for all statistical analyses. Baseline demographic variables and clinical characteristics will be compared across groups using one-way analysis of variance (ANOVA) for continuous variables and Pearson's χ^2^ tests for categorical variables. The differences in pain VAS scores and paresthesia VAS scores between the AA, sham AA, and TNM groups will be analyzed using repeated measures ANOVA with time as a repeated within-subject factor and group as a between-subject factor. Fisher's least significant difference post-hoc test will be used to compare the effects of the treatments at each time point. Sensation of needling and acceptability ratings (AAPR) will be compared across groups using one-way ANOVA. Pearson's χ^2^ tests will be used to examine the differences between groups. All tests will be two-tailed, with the significance level set at 0.05. Per-protocol (PP) analysis and intention-to-treat (ITT) analysis of the results will be conducted.

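### Paresthesia VAS is compared at each time point without its baseline value, although patients may enter at 0 mm, which costs power; a baseline covariate recovers most of it

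*Protocol article*

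**What the plan says.** Eligibility rests on pain and imaging. Section 3.1 asks for "primary complaint of unilateral leg pain radiating below the knee", an imaging-verified disc herniation, and "pain intensity score of 40 mm or more on a 100-mm visual analog scale (VAS". None of the seven inclusion criteria mentions numbness or tingling, and no exclusion criterion in section 3.2 removes patients without them.

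Section 5.2 makes paresthesia an outcome because "paresthesia (e.g., numbness and tingling) is the second most common symptom in sciatica", and anchors the scale at its lower end: "Paresthesia intensity will be assessed using a 100-mm VAS, in which “0” indicates the absence of numbness and tingling". The abstract lists it with acceptability: "The secondary outcomes will be paresthesia intensity on a VAS and the Abbreviated Acceptability Rating Profile (AAPR".

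Section 6.2 uses one model for both scales: "The differences in pain VAS scores and paresthesia VAS scores between the AA, sham AA, and TNM groups will be analyzed using repeated measures ANOVA". It continues: "Fisher's least significant difference post-hoc test will be used to compare the effects of the treatments at each time point". Per-protocol and intention-to-treat analyses are planned. The section states no baseline covariate and no analysis confined to patients who have the symptom. The abstract and section 5.3 both provide for a baseline assessment.

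**The concern.** For pain, the 40 mm entry threshold gives every patient room to improve. Paresthesia has no such threshold. A patient without numbness or tingling is eligible, starts at 0 mm, and can only stay there or get worse.

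Two things follow when raw scores are compared between groups at a given time:

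- The mean difference is the effect in symptomatic patients multiplied by the symptomatic share.
- The scores mix a cluster at 0 mm with a symptomatic distribution well above it. That adds between-patient variance unrelated to treatment, and chance differences between groups in who has the symptom carry straight into the group means.

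At stake is how a paresthesia result can be read. A null finding could reflect an insensitive comparison. A modest observed difference could partly reflect who had the symptom at entry.

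**Working it through.** **What can be taken from the protocol.** Section 6.1 gives 26 evaluable patients per group and a two-sided 5% level. That number was set for pain. It cannot be reproduced, because no effect size, SD or correlation is stated. Nothing is given for paresthesia: no share with the symptom, mean, SD or effect. The rest is therefore an illustration on assumed values.

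**Assumptions.** Share p of patients have paresthesia; the others are at 0 mm at baseline and afterwards. In symptomatic patients the mean is 45 mm, the SD is 20 mm at both times, the baseline/follow-up correlation is 0.5, and treatment lowers the mean by 15 mm, from 45 to 30. The comparison is of two groups of 26 at one time point. Truncation of the symptomatic distribution at 0 mm is ignored.

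**Raw scores, all patients.** Difference = p × 15. Variance in an arm with symptomatic mean m = p × 20² + p(1−p) × m².

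- p = 0.6: difference 9 mm. Variances are 240 + 0.24 × 45² = 726 and 240 + 0.24 × 30² = 456, averaging 591, so the SD is 24.3 mm.
- p = 0.8: difference 12 mm. Variances are 320 + 0.16 × 45² = 644 and 320 + 0.16 × 30² = 464, averaging 554, so the SD is 23.5 mm.

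**Change from baseline, all patients.** Symptomatic change variance is 2 × 20² × (1 − 0.5) = 400.

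- p = 0.6: (240 + 240 + 0.24 × 15²)/2 = 267, SD 16.3 mm.
- p = 0.8: (320 + 320 + 0.16 × 15²)/2 = 338, SD 18.4 mm.

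**Baseline as covariate, all patients.** Baseline/follow-up covariance in an arm = p × 0.5 × 20² + p(1−p) × 45 × m. Residual variance = mean follow-up variance − (mean covariance)² / baseline variance.

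- p = 0.6: covariances 120 + 486 = 606 and 120 + 324 = 444, mean 525. Residual variance 591 − 525²/726 = 211, SD 14.5 mm.
- p = 0.8: covariances 160 + 324 = 484 and 160 + 216 = 376, mean 430. Residual variance 554 − 430²/644 = 267, SD 16.3 mm.

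**Baseline as covariate, symptomatic patients only.** Difference 15 mm, SD 20 × √0.75 = 17.3 mm, with on average 0.6 × 26 = 15.6 or 0.8 × 26 = 20.8 patients per group, varying by chance.

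Approximate power (the adjusted figures were obtained by simulation):

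| Analysis | 60% symptomatic | 80% symptomatic |
|---|---|---|
| Raw scores, all patients | 25% | 44% |
| Raw scores, symptomatic only | 51–53% | 64–66% |
| Change scores, all patients | 50% | 64% |
| Baseline-adjusted, all patients | 59% | 73% |
| Baseline-adjusted, symptomatic only | 62% | 76% |

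If everyone has paresthesia, raw power is 76% and adjusted power about 86% (SD 17.3 in place of 20). So part of the gain from adjustment is the usual one; the rest comes from absorbing the cluster at 0 mm.

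**Chance imbalance.** With 30 randomised per group and p = 0.6, variation in who has the symptom alone gives the difference in baseline means a standard error of 45 × √(2 × 0.6 × 0.4 / 30) = 5.7 mm, against a diluted effect of 9 mm.

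**Other assumptions.** Take an effect of 18 mm, SD 20 mm and symptomatic mean 50 mm, which give 90% power when all are symptomatic. With 30% at 0 mm, raw-score power is 43% (53% to 35% for means of 40 to 60 mm), change-score power 73%, and raw-score power in symptomatic patients only 77%. The direction is the same.

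**The case against.** The strongest reply is that section 6.2 specifies a repeated measures ANOVA. If baseline is one level of the time factor, as is usual though the section does not list the levels, the group-by-time term works on within-patient change. The stable zeros then largely cancel: 50% power in all patients at 60% symptomatic, about the same as 51–53% on raw scores in symptomatic patients only. This stands. It shows that the loss comes mainly from using raw scores, not from including patients at 0 mm. It does not remove the point, because section 6.2 also compares treatments by LSD at each time point, and no baseline adjustment is stated there.

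A reader might infer from the raw-score rows that the comparison should be restricted to symptomatic patients. The documents and the arithmetic do not support that as the main remedy. Once baseline is in the model, restriction adds about 3 points of power and changes the target population. It would also take patients at 0 mm out of the comparison, although the Introduction and section 5.2 list numbness among needling sensations, so new numbness is of interest.

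It is also fair to say that the Introduction describes sciatica as characterised by pain, paresthesia and weakness, so the share at 0 mm may be small. Being the second most common symptom does not show that many patients lack it. Covariates for a secondary outcome are often left to an analysis plan, and one may exist. The point here concerns the comparison that section 6.2 does state.

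**Conclusion.** The point holds as a matter of efficiency and interpretation. Patients without paresthesia are eligible, and time-point comparisons of raw scores let symptom status at entry add noise. The comparison remains valid under the null; type I error is not affected by this, and the primary outcome is untouched.

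On the stated assumptions, raw-score comparison gives about 25% power against 59% with baseline adjustment in all patients at 60% symptomatic, and 44% against 73% at 80%. The size depends on the share at 0 mm, which the document does not give. If nearly all patients have paresthesia, only the ordinary gain from baseline adjustment remains.

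Three stronger readings are not supported. Paresthesia is one of the secondary outcomes, and the protocol designates none of them as the main one. A false negative cannot be called the likely result, since neither the share at 0 mm nor the expected effect is known and the trial was sized on pain alone. Nor can chance imbalance be said to move the means as much as treatment does: it is random error, and its size rests on assumed values.

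**What to change.** In section 6.2, state that post-treatment paresthesia VAS will be analysed in all randomised patients with baseline paresthesia VAS as a covariate, in place of raw-score comparisons at each time point. Pre-specify a supportive analysis in patients whose baseline paresthesia VAS is above 0 mm, with the same covariate. That subset is defined by a pre-treatment value, so the comparison stays randomised. In the remaining patients, report the number with new-onset paresthesia per group.

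The cost is wording only, since the baseline reading is already planned. The supportive analysis has fewer patients, and its conclusion covers only patients who have the symptom at entry.

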### Trial design

2.1

The study is designed to be a randomized, three-arm, parallel-group, controlled trial to evaluate the immediate efficacy, safety, and acceptability of AA therapy for sciatic pain due to a herniated lumbar disc. The three arms are AA, sham AA, and traditional needle manipulation (TNM). The clinical trial is patient/assessor-blinded, thus adhering strictly to SPIRIT (Standard Protocol Items for Randomized Trials) guidelines.^[27]^ The flowchart of the study protocol is shown in Figure 1 and the trial schedule is shown in Figure 2.

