### Data collection and management

5.3

To evaluate the effect of AA, data will be collected at baseline, upon completion of the intervention, and at short-term follow-up (days 3 and 7 after acupuncture). The data items and the corresponding timeline are summarized in Table 1. A case report form (CRF) has been designed to include the variables of interest. To increase the objectiveness of subsequent statistical analysis, the information obtained by CRF will be transcribed to an electronic database by 2 independent researchers; any disagreement will be solved by discussion. To protect confidentiality of participants, initials will be recorded in CRFs, and all CRFs will be stored in a locked cabinet in Shanghai University of Traditional Chinese Medicine, and will have a unique identification number. The access to the database will be restricted to the researchers in this study team.

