## Discussion

7

AA has been recognized as a readily available and valuable means of health care. Different from traditional acupuncture, AA penetrates the skin and inserts the needles shallowly in the subcutaneous tissue above the ankle, with no characteristic needle-manipulation sensation. Therefore, the procedure is not only effective, but also requires only simple equipment and is inexpensive, relatively safe, convenient, and quick. However, the practice of AA is still mainly based on personal experience. Further clinical research on AA will provide additional evidence to confirm its effectiveness, thereby enhancing its acceptance and utilization. The purpose of this study is to evaluate the immediate effect of ankle acupuncture for sciatica associated with a herniated lumbar disc. We propose the following specific aims: (1) to determine if patients receiving AA show significant improvements in pain as measured by VAS compared to control patients; and (2) to determine the safety and acceptability of AA therapy by assessing its possible adverse effects and acceptability ratings after one session of treatment. One of the strengths of our study is that it is designed to be a feasible, comparative effectiveness trial design that is similar to common clinical situations. The results of this study will determine if AA is an effective therapy for sciatica due to a herniated lumbar disc.

There is considerable evidence to show that acupuncture treatment produces pain relief for durations that outlast the period of stimulation.^[36]^ These prolonged effects after cessation of acupuncture stimulation may undergo 2 phases: (1) sudden, dramatic relief of pain for several hours after stimulation, and (2) gradual pain relief that returns days or weeks after a single treatment session.^[37]^ In this study, we will observe the duration of pain relief to provide information as to how long pain relief lasts after a single session of AA. We will set 2 follow-up time points: 3 and 7 days. Multiple time points will be used to reflect the time-effect of AA for sciatica associated with a herniated lumbar disc. Additional post-treatment measurements after single session of AA therapy will provide useful information to make definitive inferences about the clinical relevance and the underlying physiological mechanism of AA.

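### Section 5.2, as worded, covers only severe adverse events during needling, which is narrower than the safety aim and the abstract

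*Protocol article*

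**What the plan says.** Safety appears as a purpose in two places. Section 2.1 (Trial design) describes a "controlled trial to evaluate the immediate efficacy, safety, and acceptability of AA therapy for sciatic pain due to a herniated lumbar disc". The Discussion (section 7) gives as the second specific aim "to determine the safety and acceptability of AA therapy by assessing its possible adverse effects and acceptability ratings after one session of treatment". Neither statement limits the severity of the events.

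The Method paragraph of the abstract is equally broad: "The success of blinding will be evaluated, and the needle-induced sensation and adverse events will be recorded". It adds: "All outcomes will be evaluated before, during, and after the treatment".

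In the methods shown, adverse events are addressed only in section 5.2 (Secondary outcome measures): "Any severe adverse events such as bleeding, hematoma, or fainting during the acupuncture process will be observed and dealt with immediately". The sentence after it says that the needle is taken out if such an event occurs. For the follow-up contacts, section 5.2 names one item to ask about, namely additional treatments.

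Section 5.3 (Data collection and management) fixes the contacts: "data will be collected at baseline, upon completion of the intervention, and at short-term follow-up (days 3 and 7 after acupuncture". On content it refers elsewhere: "The data items and the corresponding timeline are summarized in Table 1". The body of Table 1 is not in the text available, nor is Figure 2, the trial schedule.

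**The concern.** Section 5.2 sits among the secondary outcomes and is the only place in the methods shown that says which adverse events are looked for. It is restricted twice: by severity (severe) and by time (during the acupuncture process). The aim and the abstract carry neither restriction. Two people working from this article could therefore collect different data, and the results could be reported under either scope.

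If section 5.2 is followed literally, mild events and events that emerge after needle withdrawal are not counted. For needling, the relevant ones are a bruise that shows later or an infection at the site. A report of few or no adverse events would then partly reflect the window of observation. The three arms may also be affected unequally. Sections 3.5 and 4.1 to 4.3 describe AA and traditional needle manipulation as penetrating and sham as non-penetrating. If late puncture-related events go uncounted, the two penetrating arms would look closer to sham on safety than they are. The pain comparison is not affected.

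**Working it through.** The plan gives no safety figure to reproduce, so the main check sets the texts side by side.

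**Step 1: scope of each statement**

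- Abstract, Method: any severity; outcomes assessed before, during and after treatment; the verb is to record.
- Section 7, aim 2: any severity; after one session; the verb is to assess.
- Section 5.2: severe events; during the acupuncture process; the verbs are to observe and to deal with.

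**Step 2: what section 5.2 covers on its own.** Cross severity (severe or not severe) with timing (needle in place, or after withdrawal). This gives four combinations:

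- severe, in session: covered
- not severe, in session: not covered
- severe, after withdrawal: not covered
- not severe, after withdrawal: not covered

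One of the four is covered. The needle is retained for 20 minutes (section 4), while follow-up runs to day 7 (section 5.3). The needle-removal sentence that follows supports the in-session reading, because it presupposes a needle in place.

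**Step 3: what other parts of the plan already pick up.** Worsening leg pain is measured by the primary pain VAS, which runs to day 7 (section 5.1). Pain from needling is asked about after withdrawal, as part of the sensation measure (section 5.2). Bleeding and hematoma are named in the section 5.2 sentence, but only as severe events during the session. What remains outside is mainly mild in-session events and puncture-related events that appear later.

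**Step 4: scale, for context only.** The documents give no adverse-event rate, so rates of 1%, 5% and 10% are assumed. The arm size is n = 30 (section 6.1).

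- Expected patients with an event per arm, n × p: 30 × 0.01 = 0.3; 30 × 0.05 = 1.5; 30 × 0.10 = 3.
- Chance of at least one in an arm, 1 − (1 − p)^n: 1 − 0.99^30 = 26%; 1 − 0.95^30 = 79%; 1 − 0.90^30 = 96%.
- One-sided 95% upper bound when none is seen, 1 − 0.05^(1/n): 1 − 0.05^(1/30) = 9.5%.

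The first two lines show how many events might occur, not that they would go unrecorded. The 9.5% bound follows from the arm size and would hold under full collection too. Scope decides what it refers to: under section 5.2 alone, zero of 30 would bound only the rate of severe in-session events.

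**The case against.** The strongest reply is that section 5.2 is a response rule for the treatment room and sets no limit on recording. It contains no word such as only, and it does not mention recording. The one sentence that does mention recording is in the abstract, and it is unrestricted. A rule for acute events can coexist with general recording. In addition, Table 1 and Figure 2, where collection by visit would be listed, cannot be seen. A full protocol (version 3.0, section 2.2) and a case report form also exist, and an article commonly leaves grading and collection detail to them.

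Much of this stands. A reader might infer that the trial observes only severe in-session events, that mild and delayed events are missed, and that the safety aim cannot be answered. The documents do not support that inference. The abstract is broader, the schedule is unseen, and even the narrow wording would answer the aim in part.

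The reply does not remove the disagreement itself. The article states a scope in its outcome section, and that scope differs from its own aim and abstract. This is not a complaint about missing detail. If Table 1 already schedules adverse events at follow-up, section 5.2 is misworded. If it does not, collection falls short of aim 2. The text needs correcting in both cases.

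**Conclusion.** The point holds as an inconsistency within the article. Section 5.2 is narrower in severity and in time than the safety aim and the abstract. On section 5.2 alone, one of four severity-by-timing combinations is covered, and safety would be answered only for severe events during the session. Failure to collect the rest is not proven.

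This conclusion rests on the wording and on no assumed event rate. The 1% to 10% range only shows that, with 30 patients per arm, at least one event in an arm could be anything from unlikely (26%) to nearly certain (96%). The matter deserves correction because safety is a named aim and the remedy is cheap. It does not bear on the efficacy analysis.

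**What to change.** Reconcile the abstract, section 5.2 and aim 2 in section 7 by stating in section 5.2 that:

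- adverse events of any severity are recorded from needle insertion to day 7;
- they are asked about at assessments already planned: after needle withdrawal, at the same-day assessments, and on days 3 and 7;
- they are reported as the number and proportion of patients with an event in each arm.

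Check that Table 1 and Figure 2 agree with this wording. Leave the response to events during needling unchanged.

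The cost is one added question on the case report form at existing contacts, and a few more minor events to record.
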